## Abstract

**Background:**

Chronic pain affects approximately 12 million individuals in Germany and significantly impairs quality of life. Although multimodal treatment approaches—combining physical, psychological, and behavioral strategies—are considered the gold standard, access to specialized multidisciplinary pain treatment, including physiotherapy and psychological interventions, is often hampered by long waiting times, which highlights the need for scalable, low-threshold treatment options. Digital health interventions, particularly those grounded in established therapeutic models, offer a promising solution to bridge this treatment gap. The German Digital Health Care Act has opened pathways for reimbursable digital applications, such as CHRONIC, which is grounded in acceptance and commitment therapy as a third-wave cognitive behavioral therapy framework and integrates selected cognitive behavioral techniques, mindfulness-based strategies, and physiotherapy into a structured web-based program.

**Objective:**

This study protocol outlines a randomized controlled trial (RCT) aimed at evaluating the effectiveness of CHRONIC, a 12-week web-based, multimodal self-help program for individuals with chronic pain, with a focus on reducing pain intensity, reducing pain-related interference, and improving quality of life.

**Methods:**

This is a monocentric, 3-arm RCT with assessments up to 6 months after baseline. A total of 200 participants with chronic nonmalignant pain will be randomized into one of three groups: (1) intervention with individualized psychological feedback, (2) intervention with standardized computer-generated feedback, and (3) treatment-as-usual waitlist control. Weekly modules in the intervention arms include psychotherapeutic video sessions, interactive acceptance and commitment therapy–based and cognitive behavioral therapy–based exercises, mindfulness practices, and physiotherapeutic training. Outcomes will be assessed via validated self-report instruments: West Haven-Yale Multidimensional Pain Inventory for pain intensity and interference, Assessment of Quality of Life—8 Dimensions for quality of life, German version of Chronic Pain Acceptance Questionnaire for pain acceptance, Patient Health Questionnaire-9, German version for depression, and Generalized Anxiety Disorder 7-item Scale for anxiety. Data will be analyzed using mixed models for repeated measures based on the matched ~6-month assessment. Missing data will be addressed using multiple imputation.

**Results:**

Recruitment started in January 2026 and is projected to end in July 2026. As of January 22, 2026, 18 participants had been enrolled. Primary end point data collection is expected to be completed in January 2027, with primary analyses and dissemination planned for 2027.

**Conclusions:**

This study protocol describes an RCT designed to evaluate the clinical utility of CHRONIC as a scalable, low-threshold intervention for chronic pain. CHRONIC aims to address the multifactorial nature of chronic pain by integrating psychotherapeutic, physiotherapeutic, and mindfulness-based strategies into a single digital program. Future studies will be required to determine how this multimodal format compares to unimodal interventions. The findings aim to inform future digital health developments and contribute to the implementation of biopsychosocial care models in routine practice.

## Introduction

### Background

Approximately 12 million individuals in Germany are affected by chronic pain [1], representing around 14% of the national population. Alongside physiotherapy and medication, psychotherapeutic interventions have proven effective in treating chronic pain [2]. However, extensive waiting times of several months before patients receive access to specialized multidisciplinary pain services represent a major barrier to adequate pain management and contribute to delayed treatment initiation and symptom chronification [3], highlighting the urgent need for scalable, cost-effective treatment options. To address this gap, the German government implemented the Digital Healthcare Act (Digitale-Versorgung-Gesetz) on December 9, 2019, enabling physicians and psychotherapists to prescribe reimbursable digital health applications. Parallel to these developments, international research has demonstrated that digital psychological interventions for chronic pain, and particularly those based on acceptance and commitment therapy (ACT) and cognitive behavioral therapy (CBT), can effectively reduce pain interference and distress compared with waitlist control conditions [4-6]. For example, the German online ACT program ACTonPain showed medium effects on pain-related functioning and pain acceptance in individuals with long-standing pain symptoms, with improvements sustained at follow-up. Importantly, ACTonPain compared guided and unguided ACT delivery and found significant improvements in both intervention arms relative to waitlist control, while guided ACT demonstrated stronger effects and lower attrition rates, highlighting the potential clinical value of blended or therapist-supported components in digital pain treatment [4]. However, most existing digital interventions primarily reflect unimodal treatment formats focusing on psychological or physical mechanisms in isolation. Given the multidimensional nature of chronic pain and the limitations of unimodal approaches, there is a need for integrated, multimodal digital interventions that combine psychotherapeutic, behavioral, and physical activation strategies within a single framework. The rationale for developing a multimodal digital intervention is further supported by research demonstrating that chronic pain outcomes improve most when biological, psychological, and behavioral mechanisms are targeted simultaneously. Meta-analytic findings show that multimodal pain rehabilitation programs outperform unimodal approaches in terms of pain interference, disability, and emotional functioning [7,8]. Digital delivery formats are increasingly used to operationalize such biopsychosocial principles: blended or hybrid pain interventions combining psychological content, physical exercise components, and self-management strategies have reported clinically meaningful improvements in pain intensity, mobility, and quality of life [9,10]. These results suggest that integrating physiotherapeutic and psychological principles within a single digital platform may strengthen treatment effects by addressing multiple pain mechanisms concurrently rather than sequentially. The web-based application CHRONIC is designed to address this care gap for individuals with chronic pain. CHRONIC is grounded in ACT [11] as a third-wave cognitive-behavioral approach and integrates selected traditional CBT techniques (eg, cognitive restructuring and behavioral activation), mindfulness-based strategies [12], and physiotherapeutic exercises into a coherent, multimodal program. The goal is to offer a comprehensive educational and therapeutic program that equips users to manage their pain condition effectively. Given the multidimensional nature of chronic pain, a multimodal treatment approach—integrating biological, psychological, and social elements—is considered necessary [13]. Skelly et al [14] found that unimodal nonpharmacological interventions for chronic pain—such as isolated exercise or psychological therapies—often produce only modest and short-term effects. Long-term benefits were rare, and methodological heterogeneity limited the strength of evidence. The authors conclude that single-modality treatments fail to address the biopsychosocial complexity of chronic pain, highlighting the need for integrated, multimodal approaches.

### Identification and Treatment of Chronic Pain

Pain is defined by the International Association for the Study of Pain as a persistent sensation following the expected healing time of an acute injury [15]. Due to variability in recovery durations depending on the nature of the injury, clinical practice commonly applies a fixed time threshold to define chronic pain. For instance, low back pain is classified as chronic when persisting beyond 6 months, whereas postherpetic neuralgia may be considered chronic after only 3 months [16].

The *International Classification of Diseases—11th revision* has improved the classification of chronic pain by introducing clinically relevant categories and specific diagnostic criteria [17]. Chronic pain is now divided into seven distinct categories: (1) chronic primary pain, (2) chronic cancer-related pain, (3) chronic postsurgical and posttraumatic pain, (4) chronic neuropathic pain, (5) chronic headache and orofacial pain, (6) chronic visceral pain, and (7) chronic musculoskeletal pain. All categories share the criterion of persistent or recurrent pain for a minimum duration of 3 months, with optional specifiers addressing psychosocial factors and severity. The latter is assessed through pain intensity, interference, and functional limitations. Each category also emphasizes the significant impairment in quality of life and the necessity to exclude other potential etiologies before diagnosis [18].

A review by Hylands-White et al [13] outlined the diverse range of chronic pain treatments. Pharmacologic approaches such as analgesics may offer short-term relief but often show limited effectiveness in chronic nonmalignant pain. Even opioids typically reduce pain by only 30%, with potential for tolerance, side effects, and reduced long-term benefits. Nonsteroidal anti-inflammatory drugs are more effective in some cases but carry risks such as gastrointestinal bleeding and cardiovascular events, particularly with long-term or high-dose use. Topical analgesics offer lower systemic risk, though concerns regarding dependency persist—especially for opioid-based agents [19]. Adjuvant medications, including anxiolytics, hypnotics, antidepressants, and anticonvulsants (often used off-label), are also possible approaches. Nonpharmacological treatments include spinal cord stimulation, deep brain stimulation, repetitive transcranial magnetic stimulation, transcranial direct current stimulation, counter-irritation, transcutaneous or percutaneous electrical nerve stimulation, topical capsaicin, and thermotherapy or cryotherapy.

However, the inherently multidimensional nature of chronic pain necessitates a biopsychosocial framework that integrates biological, psychological, and social interventions. Physiotherapy contributes by maintaining or restoring physical function, while psychotherapeutic techniques from CBT and ACT assist patients in coping with chronic pain, implementing stress management strategies, and achieving emotional stabilization [13]. Digital interventions in chronic pain management show significant promise but require further rigorous investigation to establish their evidence base and long-term effectiveness [20,21]. Currently, in Germany, just one digital health application is officially listed and reimbursable for chronic pain treatment: “HelloBetter Chronische Schmerzen,” an interactive online program based on ACT techniques, including psychoeducation, videos, and audio [22]. This program primarily addresses the psychotherapeutic dimension of chronic pain but does not include physiotherapeutic components. Therefore, the inclusion of applications such as CHRONIC, which incorporates both physical activation and psychological guidance, would represent a valuable extension of current digital care offerings within a truly biopsychosocial framework.

### The Future Study

The aim of the future study is to evaluate the effectiveness of the digital intervention CHRONIC for individuals with chronic pain. In light of the increasing availability of web-based programs targeting chronic pain, CHRONIC adopts a multimodal approach that distinguishes itself from existing interventions by integrating multiple evidence-based components rather than relying solely on a singular therapeutic framework, thus providing a truly biopsychosocial framework. To enhance compliance and user engagement, the program incorporates a video-based therapist who guides participants through interactive modules, thereby fostering a sense of therapeutic alliance. In addition, personalized feedback is provided to further support adherence and individualization of the intervention process.

### Study Objectives

The following research questions and objectives are to be examined in the context of evaluating the 12-week web-based self-help program CHRONIC for individuals with chronic pain:

Reduction of pain intensity: Does participation in CHRONIC lead to a reduction in experienced pain intensity compared to a treatment-as-usual (TAU) group at postintervention (week 12) and the primary end point (6 mo after baseline)?Reduction of pain-related impairment: Does CHRONIC reduce the degree to which chronic pain interferes with daily life and functioning compared to TAU at postintervention (week 12) and the primary end point (6 mo after)?Improvement in quality of life: Does participation in CHRONIC enhance participants’ quality of life compared to TAU at postintervention (week 12) and the primary end point (6 mo after)?Increase in pain acceptance: Does CHRONIC support participants in developing a higher level of acceptance regarding their chronic pain compared to TAU at postintervention (week 12) and the primary end point (6 mo after)?Comparison of feedback formats: Does template-based, computer-generated feedback offer comparable benefits to individualized therapist feedback within a web-based self-help setting? Specifically, do participants receiving standardized feedback (experimental group with computer-generated feedback [EGcomp]) differ significantly from those receiving personalized feedback (experimental group with individualized psychological feedback [EGpsych]) regarding primary outcomes?

The overall aim is to evaluate the effectiveness of CHRONIC as a low-threshold, scalable intervention for individuals with chronic pain and to explore the potential of automated feedback systems within digital health interventions.

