### Study Design

This is an interventional, randomized controlled trial (RCT) with 3 parallel arms, including a nonblinded TAU group. The 2 experimental groups (EGpsych and EGcomp) complete 3 assessments: baseline prior to intervention start (T0), postintervention at week 12 (T1), and a 3-month postintervention follow-up, which represents the primary end point (6 mo after baseline, T2). In contrast, the TAU group follows an extended assessment schedule due to the 6-month waiting period: TAU participants complete a baseline measurement at study entry (T0), a second assessment following the 6-month waiting period and immediately before accessing the intervention (TAU-T1), a postintervention assessment after completing the 12-week program (TAU-T2), and a 3-month follow-up (TAU-T3). The 2 experimental groups receive access to the digital self-help program CHRONIC. Participants in the TAU group will receive access to the CHRONIC program with standardized computer-generated feedback (EGcomp version) after completing the 6-month waiting period. The 6-month waiting period for the TAU group was selected for 3 reasons. First, it reflects real-world access barriers in specialized pain services in Germany, where waiting times of 4 to 6 months are frequently reported for multidisciplinary pain treatment programs and specialist behavioral interventions, making this duration clinically realistic rather than arbitrary [3,23]. Second, extending the waiting period increases the likelihood of detecting natural symptom progression and pain chronification effects, allowing a meaningful comparison with the intervention arms and preventing artificially low variance caused by very short control periods. Third, choosing a 6-month window enables methodological alignment with the intervention design: since participants in the experimental arms undergo a 12-week treatment followed by a 3-month follow-up, the 6-month TAU period ensures comparable temporal exposure before receiving access to the program. The groups differ in the type of feedback received after each module: participants in the EGpsych receive individualized feedback written by the study team, whereas participants in the EGcomp receive standardized, template-based, computer-generated feedback. The study design is illustrated in Figure 1.

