### Statistical Analysis

All statistical analyses will be conducted using the statistical software R (version 4.5.0; R Core Team). For the PP analysis, “full adherence” will be defined a priori. Participants must complete at least 9 out of the 12 intervention modules (≥75% completion rate) within the intended 12-week intervention period to be included in the PP dataset. Thresholds such as completing ≥75% of modules are commonly reported in digital intervention research to operationalize adherence criteria, although empirical justification varies across studies, and this threshold is considered consistent with existing eHealth adherence frameworks [28]. Participants who complete fewer than 9 modules or who finish all modules in an implausibly condensed time frame that violates the intended weekly structure will be excluded from the PP dataset. First, all primary and secondary outcomes as well as participant demographics and baseline characteristics will be analyzed descriptively (means, SDs, and frequencies), both for the total sample and stratified by the study group (EGpsych, EGcomp, and TAU). To examine intervention effects, mixed models for repeated measures will be used as the primary analytic approach. The mixed models for repeated measures allow the inclusion of all available outcome data and accommodate unequal assessment schedules between groups due to the 6-month waiting period in the TAU condition. The primary randomized comparison will focus on the matched assessment approximately 6 months after baseline, corresponding to the 3-month follow-up in the experimental groups (T2) and the end of the waiting period in the TAU group (TAU-T1). For each primary and secondary outcome, models will include fixed effects for group (EGpsych vs EGcomp vs TAU), time (baseline vs matched 6-mo assessment), and the group × time interaction. A participant-specific random intercept will be included to account for within-person correlation. The group × time interaction will be used to test differential change between conditions. Holm-corrected post hoc contrasts will be applied for pairwise comparisons where applicable. If model assumptions are violated, appropriate robust methods will be considered. Outcome data collected in the TAU group after participants have received access to CHRONIC (eg, TAU-T2 and TAU-T3) will not be included in the primary randomized comparison because TAU no longer represents a control condition at that stage. Post-waitlist TAU data will instead be analyzed separately and within-group (exploratory) to describe changes following delayed program access. Exploratory analyses within each study arm will be reported descriptively. However, comparisons across nonmatched time intervals will not be interpreted as randomized sensitivity analyses. When a significant main or interaction effect is detected, Holm-corrected post hoc tests will be applied to determine the specific time points and group differences, while controlling for the family-wise error rate.

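### Objectives 1 to 4 ask for CHRONIC versus TAU at week 12, but TAU is not assessed then, so only the 6-month half of each objective can be answered

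*Protocol article*

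**What the plan says.** - **Study Objectives.** Objective 1 (pain intensity) asks for an effect "compared to a treatment-as-usual (TAU) group at postintervention (week 12) and the primary end point (6 mo after baseline". Objectives 2 to 4 (impairment, quality of life, pain acceptance) repeat both times: "compared to TAU at postintervention (week 12) and the primary end point (6 mo after". Objective 5 compares the two feedback formats and does not involve TAU.
- **Study Design.** The two experimental arms have three assessments: "baseline prior to intervention start (T0), postintervention at week 12 (T1), and a 3-month postintervention follow-up", the last of these being the 6-month primary end point. TAU has a baseline, then "a second assessment following the 6-month waiting period and immediately before accessing the intervention (TAU-T1", then "a postintervention assessment after completing the 12-week program (TAU-T2), and a 3-month follow-up (TAU-T3".
- **Statistical Analysis.** For every primary and secondary outcome the model has fixed effects for group, "time (baseline vs matched 6-mo assessment), and the group × time interaction". TAU-T2 and TAU-T3 are kept out of the primary randomized comparison because TAU has by then received the program. The section adds that "comparisons across nonmatched time intervals will not be interpreted as randomized sensitivity analyses".

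**The concern.** Week 12 is the end of treatment, and three of the four affected objectives concern the primary outcomes. The objectives promise a controlled answer at that time, but the assessment schedule collects no control data for it and the model has no place for it. These three parts of the protocol cannot all stand.

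At stake is the end-of-treatment effect against control. If week-12 results were reported under objectives 1 to 4, they could rest only on change from baseline in the experimental arms. That change mixes any treatment effect with regression to the mean and the natural course of pain.

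**Working it through.** **Step 1: set the schedule against the objectives and the model** (Study Objectives, Study Design, Statistical Analysis).

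| Time since baseline | EGpsych, EGcomp | TAU | Asked for in objectives 1–4 | Level in the model |
|---|---|---|---|---|
| 0 | T0 | T0 | – | yes |
| Week 12 | T1 | none | yes | no |
| 6 months | T2 | TAU-T1 | yes | yes |
| About 9 months (6 months + 12 weeks) | none | TAU-T2, after CHRONIC | no | no |
| About 12 months (9 + 3 months) | none | TAU-T3, after CHRONIC | no | no |

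The randomized arms share two time points, baseline and 6 months. At week 12 the number of TAU observations is 0. Four of five objectives lose one of their two stated times.

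**Step 2: look for another source of week-12 control data.**

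- TAU-T2 is also labelled postintervention, but it falls about 9 months after baseline and follows TAU's own use of CHRONIC. It is not a control measurement.
- The weekly check-ins (CHRONIC Web Application) appear when a module is opened. TAU has no modules while waiting.
- The footnote to Table 2 mentions extra TAU assessments without dating them. Study Design dates them, and none is at week 12.
- Multiple imputation cannot help. Week 12 would be missing for every TAU participant, so no observation informs that arm's mean.

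**Step 3: side check on the sample size.** Sample Size gives f = 0.20, α = 0.025, power 0.95, r = 0.50, ε = 0.75 and N = 114. It does not state the number of groups k or of measurements m, so both are assumptions here. For the within-between interaction:

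- λ = f²·N·m·ε/(1 − r)
- df1 = (k − 1)(m − 1)ε
- df2 = (N − k)(m − 1)ε

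With k = 3, m = 3 and N = 114: λ = 0.04 × 114 × 3 × 0.75/0.5 = 20.52, df1 = 3, df2 = 166.5, and power is 0.954. The smallest N is 113, rounded up to 114 for equal groups, which matches the stated figure.

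With k = 3 and m = 2, the layout of the stated model, N is 144 at ε = 0.75. It is 117 at ε = 1, the value that applies when there are only two time levels. Other layouts at the stated α and ε give 122 (2 × 2), 96 (2 × 3) and 96 (3 × 4).

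So the stated N fits a plan with three time points. This is an inference from unstated inputs, and the point does not depend on it. All three-arm figures, 114, 117 and 144, lie below the target of 200 before dropout.

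**The case against.** The strongest reply is that nothing primary is lost. Six months is named as the primary end point, TAU is assessed then before any access to CHRONIC, and the primary comparison is tied to that matched assessment. Statistical Analysis also limits misuse: analyses within an arm are reported descriptively, and nonmatched comparisons are not to be read as randomized. What remains is four objectives that were not aligned with the analysis section, and rewording would cure that. All of this stands. It narrows the point but does not remove it, because the objectives still ask a question the design cannot answer.

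A reader might infer more than the documents support:

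- **That TAU dropouts would be imputed from baseline alone while experimental-arm dropouts have T1.** No imputation model is given, so whether T1 enters it is unknown. Experimental participants who leave before week 12 have no T1 either. This is at most an assumption.
- **That the gap between 114 and 200 measures the harm.** It is an overall allowance for dropout. It is neither a TAU dropout rate nor a consequence of the missing visit.
- **That the two-level model contradicts the remark on using all available data.** That remark describes what mixed models permit. It does not promise that T1 will be a model level.

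**Conclusion.** The point holds. As written, the week-12 half of objectives 1 to 4 has 0 control observations and no randomized contrast. This follows from the stated schedule and model alone. Figure 1 is not available to check, but the text of Study Design is explicit. The gap is not a detail that could be left to an analysis plan, because no analysis can create an assessment that was not made.

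The defect is limited to week 12. The 6-month comparison with TAU is matched and can be answered. Objective 5 has week-12 data in both of its arms, although the stated model has no week-12 level for them.

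If allocation is equal, which the article does not state, the missing visit concerns about 200/3 ≈ 67 TAU participants, against up to about 133 with a week-12 assessment in the experimental arms.

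**What to change.** **Preferred.** Give TAU the same online battery at 12 weeks after baseline, before any access to CHRONIC. Fit baseline, week 12 and 6 months as three time levels, and keep the 6-month contrast primary. The cost is a short amendment and one more questionnaire for each TAU participant (about 67 under equal allocation). Timing matters: recruitment began in January 2026, with 18 enrolled by January 22, so the first TAU participants reach week 12 around April 2026. Anyone already past week 12 when the change takes effect will lack that assessment, and it cannot be recovered.

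**Otherwise.** Remove the week-12 TAU comparison from objectives 1 to 4. State that week-12 data serve only to compare EGpsych with EGcomp or to describe change within those arms. This costs only wording, but it gives up any controlled estimate at the end of treatment.

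Under either option, state the numbers of groups and measurements behind N = 114, so that the sample size, schedule and model can be seen to agree.

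### Objective 5 asks whether automated feedback is comparable to individual feedback but specifies only a test for a difference, which cannot support comparability

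*Protocol article*

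**What the plan says.** The fifth objective in the protocol article (Study Objectives) asks: "Does template-based, computer-generated feedback offer comparable benefits to individualized therapist feedback within a web-based self-help setting". The next sentence makes this operational: "Specifically, do participants receiving standardized feedback (experimental group with computer-generated feedback [EGcomp]) differ significantly from those receiving personalized feedback", with reference to the primary outcomes. The same section closes by describing the wider aim for automated feedback as "to explore the potential of automated feedback systems within digital health interventions".

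In Statistical Analysis, the model for each outcome has fixed effects for group (three levels), "time (baseline vs matched 6-mo assessment), and the group × time interaction". On testing it says: "The group × time interaction will be used to test differential change between conditions". Two sentences cover pairwise comparisons. One reads "Holm-corrected post hoc contrasts will be applied for pairwise comparisons where applicable". The other makes them conditional: "When a significant main or interaction effect is detected, Holm-corrected post hoc tests will be applied".

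The article states no equivalence or non-inferiority hypothesis, no margin, and no rule based on a confidence interval for the contrast between the two feedback arms. The Sample Size section powers the group × time interaction and does not mention this contrast.

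**The concern.** The question and the test do not match. Rejecting the null of no difference shows that the feedback formats differ. Failing to reject it shows only that the data did not settle the matter. Because *comparable* is spelled out as whether the arms differ significantly, the only outcome of the stated test that looks like a yes to the question is a non-significant result.

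Multiplicity control then works in an unhelpful direction. Holm correction protects against false claims of a difference, but it also makes a non-significant result more likely when a real difference exists. Under the conditional wording, the contrast might not be tested at all if no omnibus effect is significant.

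What is at stake is the trial's message on automated feedback. Feedback type is the stated difference between the two active arms (Study Design). The Background reports that, in a cited trial of guided and unguided delivery, the guided form had stronger effects and lower attrition. A true disadvantage for automated feedback is therefore plausible on the article's own account.

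This is more than a detail that an analysis plan would supply later, because the type of hypothesis is fixed in the objective itself.

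**Working it through.** **Inputs.** From Sample Size: f=0.20, α=.025, power .95, r=0.50, ε=0.75, minimum N=114, target N=200. From Statistical Analysis: two time points in the primary model. Assumed: 1:1:1 allocation, since the article gives no ratio. This gives 200/3, about 66 to 67 per arm without dropout, and 114/3 = 38 per arm at the minimum. Going from 200 to 114 implies a loss of 1 − 114/200 = 43%.

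**The plan's own figure.** For the within-between interaction, λ = f²·N·m·ε/(1−r), df1 = (k−1)(m−1)ε and df2 = (N−k)(m−1)ε. With k=3 groups, m=3 measurements and N=114, λ = 0.04×114×3×0.75/0.5 = 20.52, df1 = 3, df2 = 166.5, and power is 0.954. The smallest N reaching .95 is 113, which is 114 in equal groups. The stated figure is reproduced. It powers the three-arm omnibus interaction, not EGcomp versus EGpsych. It needs three measurements, whereas the primary model has two. With two time points ε is necessarily 1 and N is 115 (117 in equal groups), so that has little bearing here.

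**Precision of the feedback contrast, per outcome.** The SD of change is SD×√(2(1−r)) = SD×√(2×0.5) = 1 SD, so SE = √(2/n) in SD units.
- n=67: 1.96×√(2/67) = 0.34 SD
- n=38: 1.96×√(2/38) = 0.45 SD

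Even if the observed difference were exactly zero, losses up to those limits would not be excluded. With a non-zero but non-significant estimate, one limit lies further out.

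**Power to detect a true difference** (two-sided, noncentral t, per outcome). The documents give no difference of interest, so a range is shown.

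| True difference | 66 per arm, .05 | 66 per arm, .0167 | 38 per arm, .05 |
|---|---|---|---|
| 0.2 SD | 21% | 10% | 14% |
| 0.3 SD | 40% | 25% | 25% |
| 0.4 SD | 63% | 45% | 41% |
| 0.5 SD | 81% | 67% | 58% |

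The level .0167 is .05/3, the strictest Holm step for three pairwise contrasts. On a single outcome at an uncorrected .05, a true 0.3 SD disadvantage would be non-significant about 60% of the time with 66 per arm and about 75% with 38.

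**What a comparability claim would need.** Non-inferiority power with a true difference of zero is Φ(margin/SE − 1.96). At margins of 0.2, 0.3, 0.4 and 0.5 SD this gives 21%, 41%, 63% and 82% with 66 per arm, and 14%, 26%, 41% and 59% with 38. For 80% power, the completers needed per arm at those margins are 393, 175, 99 and 63.

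**The case against.** The strongest reply is that the article never says a null result will be reported as comparability. Its operative sentence asks a coherent question about a difference, and its Conclusions, Discussion and Limitations claim no equivalence. The aim for automated feedback is worded as exploratory, the first four objectives concern CHRONIC against treatment as usual, and a margin is needed only if comparability is to be claimed. This stands. A reader might infer that the plan will declare the formats comparable because of low power alone, but the document does not support that: it is a risk created by the pairing of question and test, not a stated rule. A reader might also infer that showing comparability is the reason for having two active arms. The article does not say so, and it also uses the two arms to compare adherence and dropout.

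The figures can also be challenged. They are per outcome, and there are three primary outcomes. If a 0.3 SD loss applied to all three, each tested at .05, the chance that none is significant is about 34% (67 per arm) to 53% (38 per arm) at an assumed between-outcome correlation of 0.5, and 20% to 41% at zero correlation. The 38-per-arm case needs 43% attrition, and 0.3 SD is illustrative. These limits stand too, which is why the figures are shown as ranges.

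The reply does not remove the mismatch. Objective 5 is a listed research question on the primary outcomes, it is not itself labelled exploratory, and it uses the word *comparable*.

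**Conclusion.** The point holds as a mismatch between question and test: objective 5 asks for comparability, and the only test given can support nothing but a difference. How a non-significant result will be interpreted is not stated.

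The size depends on assumptions. With equal allocation and r=0.50, the feedback contrast on one outcome is estimated to within 0.34 SD with no dropout and 0.45 SD at the minimum sample. Power to detect a moderate difference such as 0.3 SD is well under one half in both cases. A non-significant contrast would therefore say little about comparability. It does not follow that comparability is out of reach: at a 0.5 SD margin with 66 per arm, non-inferiority power is 82%, and at 0.2 SD it is 21%. The answer turns on a margin that the article does not give.

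**What to change.** - Reword objective 5 as an exploratory estimation question: how large is the difference between the two feedback formats on each primary outcome?
- Report EGcomp minus EGpsych with its 95% CI on each primary outcome, whatever the omnibus test shows.
- State that a non-significant contrast will not be interpreted as comparability.
- Use the word *comparable* only if the CI excludes a margin fixed and justified, in instrument points, before the data are seen. If no such claim is wanted, no margin is needed.

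The cost is a few sentences, plus the choice of a margin if one is wanted. No participants or assessments are added. The Results section expects primary end point data to be complete in January 2027, so the change can be made before results are known. The downside is that, depending on the margin, the trial may be unable to claim comparability.
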